## 10.2 IMCF Cambodia workplan

|                                                  | 2012 |   |   |   |   |   |   |   |   |    |    |    | 2013 |   |   |   |   |   |   |   |   |    |    |    | 2014 |   |   |   |   |   |   |   |   |    |    |    |   |   |
|--------------------------------------------------|------|---|---|---|---|---|---|---|---|----|----|----|------|---|---|---|---|---|---|---|---|----|----|----|------|---|---|---|---|---|---|---|---|----|----|----|---|---|
|                                                  | 1    | 2 | 3 | 4 | 5 | 6 | 7 | 8 | 9 | 10 | 11 | 12 | 1    | 2 | 3 | 4 | 5 | 6 | 7 | 8 | 9 | 10 | 11 | 12 | 1    | 2 | 3 | 4 | 5 | 6 | 7 | 8 | 9 | 10 | 11 | 12 |   |   |
| Literature Review                                |      |   | X | X | X | X | X |   |   |    |    |    |      |   |   |   |   |   |   |   |   |    |    |    |      |   |   |   |   |   |   |   |   |    |    |    |   |   |
| Refindresearch design                            |      |   | X | X | X | X | X |   |   |    |    |    |      |   |   |   |   |   |   |   |   |    |    |    |      |   |   |   |   |   |   |   |   |    |    |    |   |   |
| Baseline Survey I                                |      |   |   |   |   |   |   | X | X |    |    |    |      |   |   |   |   |   |   |   |   |    |    |    |      |   |   |   |   |   |   |   |   |    |    |    |   |   |
| Baseline I analysis&report                       |      |   |   |   |   |   |   | X | X | X  |    |    |      |   |   |   |   |   |   |   |   |    |    |    |      |   |   |   |   |   |   |   |   |    |    |    |   |   |
| Midtermsurvey                                    |      |   |   |   |   |   |   |   |   |    |    |    |      |   | X |   |   |   |   |   |   |    |    |    |      |   |   |   |   |   |   |   |   |    |    |    |   |   |
| Midterm survey results analysis and              |      |   |   |   |   |   |   |   |   |    |    |    |      |   |   |   | X | X | X | X |   |    |    |    |      |   |   |   |   |   |   |   |   |    |    |    |   |   |
| Impact assessmentsurvey                          |      |   |   |   |   |   |   |   |   |    |    |    |      |   |   |   |   |   |   |   |   |    |    |    |      |   |   |   | X |   |   |   |   |    |    |    |   |   |
| Impact assessment analysis and report            |      |   |   |   |   |   |   |   |   |    |    |    |      |   |   |   |   |   |   |   |   |    |    |    |      |   |   |   |   | X | X | X | X | X  | X  | X  | X | X |
| Workshop: discussionofresults                    |      |   |   |   |   |   |   |   |   |    |    |    |      |   |   |   |   |   |   |   |   |    |    |    |      |   |   |   |   |   |   |   |   | X  |    |    |   |   |
| Analysis and research write-up and dissemination |      |   |   |   |   |   |   |   |   |    |    |    |      |   |   |   |   |   |   |   |   |    |    |    |      |   |   |   | X | X | X | X | X | X  | X  | X  | X |   |
| Presentingdissertation                           |      |   |   |   |   |   |   |   |   |    |    |    |      |   |   |   |   |   |   |   |   |    |    |    |      |   |   |   |   |   |   |   |   |    |    |    |   | X |

## 10.3 Participants Card

| Women 18-45 years:      |                       |
|-------------------------|-----------------------|
| Hemoglobin (Hb, g/dl)   |                       |
| < 8                     | Severe anaemic        |
| < 11                    | Anaemic               |
| 12                      | Normal (non-pregnant) |
| 11                      | Normal (pregnant)     |
| BMI                     |                       |
| < 18.5                  | Underweight           |
| 19 – 25                 | Normal                |
| 25 – 30                 | Overweight            |
| > 30                    | Obese                 |
| Children under 2 years: |                       |
| WAZ                     | HAZ                   |
| 0                       | 0                     |
| <-2                     | <-2                   |
| <-3                     | <-3                   |
| Children 6-23 months:   |                       |
| Hemoglobin (Hb, g/dl)   |                       |
| < 7                     | Severe anaemic        |
| < 11                    | Anaemic               |
| ≥                       | Normal                |

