## 4 Hypothesis

Assuming that behavior change messages on breastfeeding and complementary feeding practices as well as hygiene aspects as generated by the TIPs are widely accepted and out into practice by the mothers with children ages 0-23 months the data assessment will be based on the following hypotheses:

1. The Height for age Z-Score (HAZ) of children below 2 years will increase if TIPs recommendations and recipes are locally available and accepted. At conclusion of the intervention, there will be a difference of 15% of the HAZ between interventions and controls:

$$H0: \mu \text{ HAZ (intervention)} = \mu \text{ HAZ (control)}$$

$$H1: \mu \text{ HAZ (intervention)} > \mu \text{ HAZ (control)}$$

2. Secondly, prevalence of anemia, vitamin A deficiency as well as morbidity rates will be reduced:

a) Anemia (A) among children between 6 and 23 months, defined as hemoglobin level of < 11g/dl, will decrease by 25 %:

$$H0: P(A| \text{intervention}) = P(A| \text{control}),$$

$$H1: P(A| \text{intervention}) < P(A| \text{control})$$

b) Retinol binding protein (RBP) levels will decrease by 15% among children with a C-reactive protein (CRP) level of < 12mg/l:

$$H0: \mu \text{ RBP (intervention)} = \mu \text{ RBP (control)},$$

$$H1: \mu \text{ RBP (intervention)} < \mu \text{ RBP (control)}$$

c) Prevalence of children with presumed acute respiratory infections and fever (ARI) and diarrhea (D) in the last two weeks prior the survey will decrease by 25%:

$$H0: P(ARI| \text{intervention}) = P(ARI| \text{control}),$$

$$H1: P(ARI| \text{intervention}) < P(ARI| \text{control})$$

$$H0: P(D| \text{intervention}) = P(D| \text{control}),$$

$$H1: P(D| \text{intervention}) < P(D| \text{control})$$

d) There will be differences in knowledge of age-appropriate complementary feeding (KCF) of children between caretakers measured using a knowledge score in interventions and controls.

H0:  $\mu$  KCF (intervention) =  $\mu$  KCF (control),

H1:  $\mu$  KCF (intervention) >  $\mu$  KCF (control).

e) TIPs formative research generates nutritionally improved, culturally acceptable and affordable recipes which result in improved feeding practices and food intake which will result in a higher dietary diversity score for the children.

There will be differences in dietary diversity (DD) between interventions and controls:

H0:  $\mu$  DD (intervention) =  $\mu$  DD (control),

H1:  $\mu$  DD (intervention) >  $\mu$  DD (control).

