## 6.2 Participants

Knowing that recommendations on exclusive breastfeeding are included into the behavior change strategies all households with children 0-23 months of age are eligible to participate in the surveys. During the total data assessment period, families with children with a WAZ or WHZ-score  $<-2SD$  or sick children will be send for nutrition counseling and/ or treatment according to the countries guidelines.

Inclusion and exclusion criteria for participating in the surveys are:

- being resident in the sampled area,
- having at least one child 0 – 23 month of age,
- being randomly selected,
- accepting that anthropometric measurements and blood samples will be taken.

Families with a child who does not have a written record of the child's date of birth or the date is not known by anyone in the family or who's age cannot be estimated based on a seasonal calendar of local events around one month will be excluded from the study (see chapter 6.8.3).

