### **6.7.1 Recruitment, risks and benefits**

List of possible eligible participants will be obtained from official population's list.

There is no risk to the participants involved in the study.

**Benefits to Participants:** This study has an indirect benefit to the participants. The study does provide an opportunity for the participants to gain information about their and their children's current nutritional and health status. Participants will receive a "Participants-Card" including their and their children's health data available directly in the field (anthropometric data, age and hemoglobin level). The card will provide information whether the anthropometric measurements or the measured hemoglobin level indicate poor nutritional status. In case of abnormal results participants will be sent for nutrition counseling/ or treatment according to the guidelines of Cambodia for treatment of anemia and malnutrition.

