## **6.8 Data collection**

The data collection in the cross sectional surveys will be based on an adaptation of the SMART methodology (49). The SMART methodology includes a questionnaire designed to assess mortality, nutritional status and food security in crisis situations. The final questionnaire will consist of standardized modules extracted from the questions designed by the SMART initiative, FAO, WHO, GIZ, and the Manoff Group (1, 6, 49, 54,55-59). Thus, mothers/caretakers with children below two years will be interviewed about their socio-economic situation, food security, mothers' and children's food intake, care, time availability, access to health, water and sanitation, motor milestones, and access to FAO food security activities by trained enumerators. Anthropometric measurements will be taken from mothers, their children below two years of age, and, if possible from fathers, by a nutritionist especially trained in anthropometric measurements. Capillary blood samples will be taken from the surveyed mothers (Hb only) and children below two years to assess the micronutrient status (retinol binding protein (RBP), transferrin receptor (TfR), hemoglobin as well as the morbidity status (C-reactive protein (CRP), acyl glycoprotein (AGP) by medical trained research staff.

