#### **6.8.4 Blood samples**

Blood samples will be taken at the central weighing and measuring station. A medical technical assistant from Cambodia will obtain the blood sample for the biochemical parameters via a finger prick using sterile disposable micro lancets to obtain capillary blood.

The analysis of biochemical measurement will include assessment of retinol binding protein (RBP), hemoglobin, transferrin receptor (TfR), acyl glycoprotein (AGP) and C-reactive protein (CRP). RBP, TfR, AGP and CRP will be analyzed using sandwich ELISA technology (63). With this technology it is possible to combine the measurements of the four proteins (TfR, RBP, CRP, AGP). Instead of using four different ELISA methods with different chemicals and procedures only one method is used. This also reduces the necessary amount of blood. A plasma volume of 2 times 7.5 µl is sufficient to do a double measurement of all four proteins. Directly after taking the blood samples they will be centrifuged and serum/plasma is stored in 0.2 mL PCR tubes. These tubes can also be directly used in an automatic pipettor to avoid the tedious and error prone manual pipetting. Samples will be stored on ice in a high efficient styrofoam box with more than 5 cm thick walls and tightly closing lid. All blood samples will be stored on ice until the end of the survey. Analysis of blood samples will be done by [name], DBS-Tech, Germany.

Hemoglobin concentration will be assessed immediately at the field site with a portable HemoCueHb301\* analyzer (HemoCue, Grossostheim-Germany) following operating guidelines (HemocueHb 301+ operating manual. HemoCue GmbH, Grossostheim, Germany).

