### Conclusion

Nutritional status of mother alarming? no ☐ yes ☐

Nutritional status of child alarming? no ☐ yes ☐

→ If yes, please contact the next health post

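### The Participants-Card splits the normal haemoglobin level for women by pregnancy but not the anaemia cut-off, so as extracted a non-pregnant mother at 11.0–11.9 g/dl is below normal yet not flagged as anaemic (minor)

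*Protocol*

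**What the plan says.** Protocol section 6.8 provides for maternal haemoglobin: "Capillary blood samples will be taken from the surveyed mothers (Hb only"). Section 6.8.4 adds that "Hemoglobin concentration will be assessed immediately at the field site", so the result is available while the mother is present.

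Section 6.7.1 offers the card as a benefit of taking part: "The card will provide information whether the anthropometric measurements or the measured hemoglobin level indicate poor nutritional status". Participants with abnormal results are sent for counselling or treatment "according to the guidelines of Cambodia for treatment of anemia and malnutrition".

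Annex 10.3 sets out the bands. Under women of 18–45 years the haemoglobin rows, in g/dl, are:

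- below 8: severely anaemic
- below 11: anaemic
- 12: "Normal (non-pregnant")
- 11: normal when pregnant

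The card's conclusion asks for a yes or no on whether the mother's nutritional status is alarming, followed by "If yes, please contact the next health post".

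**The concern.** Whoever drafted the card recognised that the normal level depends on pregnancy and gave two values for it. The anaemia row was not split in the same way. A non-pregnant mother with, say, 11.5 g/dl is therefore below the level the card calls normal for her and above the level it calls anaemic.

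At stake is the consistency of a participant-facing threshold. The card is meant to tell the mother whether her haemoglobin indicates a problem, and staff must then tick yes or no. With no class for this interval, two members of staff could tick differently for the same reading, and one mother would be advised to go to the health post while another would not.

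**Working it through.** The protocol gives no calculated figure to reproduce here. The check is whether the card's rows cover every haemoglobin value.

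**Inputs (annex 10.3, women).** Severely anaemic below 8; anaemic below 11, with no pregnancy qualifier; normal at 12 if not pregnant; normal at 11 if pregnant. The two normal rows show no comparator in the extracted text. I read them as lower limits (12 or more, 11 or more), which is an assumption.

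**Coverage by pregnancy status.**

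| Hb (g/dl) | Pregnant | Not pregnant |
|---|---|---|
| below 8 | severely anaemic | severely anaemic |
| 8 to below 11 | anaemic | anaemic |
| 11 to below 12 | normal | no row applies |
| 12 or more | normal | normal |

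Width of the unclassed interval = normal level − anaemia cut-off:

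- pregnant: 11.0 − 11.0 = 0 g/dl
- not pregnant: 12.0 − 11.0 = 1.0 g/dl

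Classifying every value from 5.0 to 15.9 g/dl in steps of 0.1 gives the same answer: ten unclassed values for non-pregnant women (11.0, 11.1, …, 11.9) and none for pregnant women.

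**Sensitivity to the lost comparators.** Reading the non-pregnant row as strictly above 12 adds 12.0 itself to the unclassed values. Reading it as an upper limit would make low haemoglobin normal, which cannot be meant. No sensible comparator closes the interval.

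**Is a cut-off given elsewhere?** Section 4 has anaemia "defined as hemoglobin level of < 11g/dl", but for children of 6–23 months. The numerical referral rule in section 6.2 concerns weight-based z-scores of children, and "sick children will be send for nutrition counseling and/ or treatment according to the countries guidelines". Section 6.7.1 names the national guidelines without giving a threshold. Annex 10.3 is therefore the only place in the protocol with haemoglobin cut-offs for women.

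**Effect of the remedy.** With anaemic defined as below 12 for non-pregnant and below 11 for pregnant women, both widths are zero (12.0 − 12.0 and 11.0 − 11.0) and every value has a class.

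**The case against.** **The table is damaged.** Two comparators are missing, and the last haemoglobin row for children has a comparator without a number. A pregnancy qualifier or a further row for women could have been lost in the same way. This stands as a caveat: the point describes the card as extracted and should be checked against the original page. The extracted anaemia row is nevertheless complete in itself, and nothing visible suggests a missing neighbour.

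**The card is not a full partition anyway.** The body mass index bands go from below 18.5 to 19–25, and the z-score lists name only 0, below −2 and below −3. On this view the card gives reference points beside a measured value and need not label every value. That is fair as a description of its style. It does not remove the mismatch: where the card itself sets a pregnancy-specific normal level, a reader expects a matching anaemia level, especially with a yes/no question to follow.

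**The consequence is largely contained.** The trigger in section 6.7.1 is an abnormal result, not the word anaemic. A reading of 11.5 is recorded on a card that shows 12 as normal, and treatment follows national guidelines. This stands, and it is why the point is minor.

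**Stronger readings that the documents do not support.** A reader might infer that the card wrongly clears these mothers. It does not: it never calls 11.0–11.9 normal for a non-pregnant woman, and no text ties the alarming answer to a particular row. A reader might also infer that many mothers are affected, but the protocol gives no distribution of maternal haemoglobin, so no share can be stated. Finally, a reader might infer that the card lacks an entry for the mid-upper arm circumference that section 6.8.2 has measured in pregnant women. Part of the card is not in the text available for review, so that cannot be concluded.

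**Conclusion.** The point holds as a minor inconsistency in a participant hand-out. As extracted, the bands for women leave an interval of 1.0 g/dl, 11.0–11.9, without a class for non-pregnant mothers and no such interval for pregnant mothers. In that interval the card shows a value below its own normal level but gives no class on which to base the alarming answer and the health-post advice.

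This rests on two assumptions: that the normal levels are lower limits, and that no row or qualifier was lost from the anaemia entry in extraction.

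Only feedback to mothers, and possibly their referral, is affected. A reader might infer that the trial's anaemia result is at risk. It is not: that hypothesis concerns children of 6–23 months with their own cut-off in section 4, and no hypothesis in the protocol uses maternal haemoglobin. The primary outcome and the sample size are untouched.

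**What to change.** In annex 10.3, replace the single anaemia row for women with two rows that meet the normal levels already printed: below 12 g/dl for non-pregnant women and below 11 g/dl for pregnant women. Alternatively, print the cut-offs of the Cambodian guideline to which section 6.7.1 refers, so that card and referral use one standard.

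The cost is one changed row on the hand-out. Haemoglobin is already measured and read on site, so no new measurement is needed. The downside is some additional referrals of mildly anaemic non-pregnant mothers.

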### Interview

Household and food security situation ☐

Child feeding practices ☐

### Clinical part

Anthropometric measurements ☐

Test for edema (child) ☐

Assessment of motor milestones of child ☐

Hemoglobin prick test, mother ☐

Hemoglobin prick test, child ☐

Blood test for vit A & iron status, child ☐

### Results of anthropometry and hemoglobin

|        | Height (cm)          | Weight (kg)          | BMI (kg/m  ) | Hb (g/dl)            |
|--------|----------------------|----------------------|--------------------------|----------------------|
| Mother |  |  |      |  |
| Father |  |  |      |  |

| Age of child (months) | Height (cm)          | Weight (kg)          | WAZ                  | HAZ                  |
|-----------------------|----------------------|----------------------|----------------------|----------------------|
|   |  |  |  |  |

Edema: no ☐ yes ☐ Hb (g/dl)

### Conclusion

Nutritional status of mother alarming? no ☐ yes ☐

Nutritional status of child alarming? no ☐ yes ☐

→ If yes, please contact the next health post

## 10.4 Intra-class correlation and minimal detectable effect size (Reference 77)

[figure not shown][figure not shown]

## 10.5 Budget IMCF Cambodia

| Component Description             | year 1    | year 2   | year 3    | total            |
|-----------------------------------|-----------|----------|-----------|------------------|
| Interviewers and translators      | 20.000,00 | 0,00     | 20.000,00 |                  |
| Sub-total staff                   | 20.000,00 | 0,00     | 20.000,00 | 40.000,00        |
| Interviewer training              | 5.000,00  | 0,00     | 5.000,00  |                  |
| Sub-total training                | 5.000,00  | 0,00     | 5.000,00  | 10.000,00        |
| Local transport (lumpsum)         | 5.000,00  | 2.500,00 | 5.000,00  |                  |
| Sub-total travel                  | 5.000,00  | 2.500,00 | 5.000,00  | 12.500,00        |
| Expendable equipment for surveys  | 3.700,00  | 0,00     | 3.700,00  |                  |
| Subtotal Expendable Equipment     | 3.700,00  | 0,00     | 3.700,00  | 7.400,00         |
| Technical instruments             |           |          |           |                  |
| Office equipment                  |           |          |           |                  |
| Subtotal Non Expendable Equipment |           |          |           |                  |
| Ethical Commission fee (US\$)     | 400,00    |          |           | 400,00           |
| Total US\$                 |           |          |           | 70.300,00 |
